
### Safety assessments

We will count adverse events during the trial. Adverse events will be defined as any adverse medical reactions that have occurred from the time the subject signed the informed consent form to the time of the last follow-up, whether or not there is a causal relationship with the study treatment. All adverse effects will be assessed by the Treatment Emergent Symptom Scale. We will record the time point, severity, measures taken, whether it is related to treatment, and prognosis of adverse events (45). Investigators will assess the possible relationship of adverse events to this study and provide appropriate treatment and guidance.

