RLS can occur at any age, but with age, the prevalence increases year by year. Based on a population-based survey, the prevalence of RLS is 3% between 18 and 29 years, 10% between 30 and 79 years, and 19% in individuals older than 80 years (3). The prevalence is higher in women than in men (2, 4). RLS has both sensory and motor symptoms. The typical clinical symptom group mainly appears at night, which seriously interferes with sleep, causing difficulty falling asleep and increasing the number of night awakenings, and then fatigue, memory loss, depression, and blood pressure fluctuations, which affects the quality of life. Various functions during the day are also negatively affected (5–7). A systematic retrospective analysis of RLS (8) has shown that the prevalence of patients with anxiety and depression increases significantly. Our previous research has also shown the impact of RLS on physical and mental exhaustion during the day. Patients with RLS have obvious mood disorders such as anxiety and depression. It has been further confirmed in the Chinese population that RLS can significantly increase the risk of mood disorders (9), and an increasing number of studies have shown that RLS can increase the risk of cardiovascular disease (10, 11). Currently, Chinese scholars are also conducting large cohort studies on the potential association between RLS and cardiovascular diseases, which will provide more evidence for the intervention of related diseases in the future (12). RLS is not uncommon in clinical practice, and it is particularly worth noting in the context of Parkinson’s disease and RLS, where the prevalence of nighttime problems including probable rapid eye movement sleep behavior disorder and RLS is 9.5%, significantly higher than the prevalence of any other combination of sleep disorders (13). Because patients have low awareness of the disease, only a minority of patients with RLS go to hospital for treatment. The diagnosis is mainly based on clinical symptoms and lacks specificity. Therefore, the current diagnosis rate of the disease is relatively low. RLS is often misdiagnosed as arthritis, peripheral neuropathy, insufficient blood supply to the lower limbs, and neurosis, resulting in delayed diagnosis and treatment (14, 15). At present, the drugs used to treat RLS mainly include dopaminergic drugs, antiepileptic drugs, benzodiazepines, and opioids. However, long-term use of benzodiazepines can easily cause drug dependence, while long-term use of antidepressant or anxiolytic drugs can cause many adverse reactions. As a new generation of non-ergot dopamine receptor agonists, pramipexole not only has high specificity for dopamine receptors but also has complete intrinsic activity. It is approved for the treatment of RLS (16). However, the rebound phenomenon is the main complication of long-term use of dopaminergic drugs (17). According to research reports, the incidence of the rebound phenomenon is 27.1% in RLS patients treated with levodopa and 6.0% in RLS patients treated with pramipexole (18). Due to the low rate of correct diagnosis and treatment of RLS and the lack of long-term effective drug treatment, there is an urgent need for a treatment method with definite curative effects and few side effects.

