## Methods

### Study design

This is a randomized, single-blind, placebo-controlled clinical trial, aimed at evaluating the efficacy and safety of acupuncture for RLS patients and comparing the effects between acupuncture care and sham acupuncture care. The trial will be performed at Yueyang Hospital of Integrated Traditional Chinese and Western Medicine of Shanghai University of Traditional Chinese Medicine. We will recruit 124 patients who meet the inclusion criteria and randomly assign them to either the acupuncture or sham acupuncture groups. Basic information and baseline data will be collected in the first week after enrollment, after which the participants will enter a 1-month observation period in this trial. All treatments will be given three times a week (every other day) for 4 weeks.

The participants will be assessed at the following time points: the baseline (1 week before the treatment), the middle of the treatment (2 weeks after the treatment start), the end of the treatment (4 weeks after the treatment start), and the follow-up (1 month and 3 months after the treatment end). We will use subjective scales and polysomnography combined with functional imaging technology for comprehensive evaluation of clinical efficacy. We will use the International Restless Legs severity rating scale (IRLSS) to evaluate the symptoms of restless legs and the RLS Quality of Life (RLSQoL) to evaluate the patients’ quality of life. Insomnia Severity Index (ISI), and the Pittsburgh Sleep Quality Index (PSQI) will be used to evaluate the patients’ sleep status, and the Hamilton Depression Scale (HAMD) and Hamilton Anxiety Scale (HAMA) will be used to evaluate the mood of the patients. We will use polysomnography (PSG) to analyze the objective sleep quality of the patients, and fMRI and PET-CT will be used to monitor brain function. The detailed trial process is shown in **Figure 1** and **Table 1**. This study will follow the Consolidated Standards of Reporting Trials (CONSORT) (34) and the Standards for Reporting Interventions in Clinical Trials of Acupuncture (STRICTA) (35) guidelines for designing and reporting controlled trials.

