**Figure 1 f1:**
[figure not shown]
Flow chart.

**Table 1 T1:** Trial process chart.

	Baseline		Treatment phase				Follow-up phase	
	Week	Week	Week	Week	Week	Week	Month	Month
	-1	0	1	2	3	4	1	3
Patients								
Telephone reservation	×							
Enrollment	×							
Signed informed consent		×						
Clinical interview		×						
Physical examination		×						
Laboratory test		×						
Randomization		×						
Groups								
Acupuncture group			12 treatments					
Control group			12 treatments					
Primary outcomes								
**IRLSS**		×		×		×	×	×
Secondary outcomes								
RLSQoL		×		×		×	×	×
ISI		×		×		×	×	×
PSQI		×		×		×	×	×
HAMD		×		×		×	×	×
HAMA		×		×		×	×	×
PSG		×				×		
PET-CT		×				×		
fMRI		×				×		
TESS			×	×	×	×		
Drug dose record		×	×	×	×	×	×	×
Patient’s compliance			×	×	×	×	×	×

IRLSS, the International Restless Legs severity rating scale; RLSQoL, the RLS Quality of Life; ISI, the Insomnia Severity Index; PSQI, Pittsburgh Sleep Quality Index; HAMD, Hamilton Rating Scale for Depression; HAMA, Hamilton Anxiety Sale; PSG, polysomnography; PET-CT, Positron Emission Tomography-Computed Tomography; fMRI, functional magnetic resonance imaging; TESS, Treatment Emergent Symptom Scale.

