### Interventions

All acupuncturists are licensed doctors with 10–15 years of experience in acupuncture treatment, and they will participate in the training before the intervention to ensure the standard real and sham acupuncture operations. The participants in the treatment group and the control group will receive acupuncture and sham acupuncture treatments, respectively. The participants in these two groups will receive 12 sessions of different treatments, three times a week for 4 weeks. After skin cleansing, the patients will lie on their back and receive acupuncture or sham acupuncture treatment. Each treatment will last for 30 min. The temperature of the treatment room will not be lower than 26°C.

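### TESS, the scale named for all adverse effects, has no reading before treatment, so symptoms present at entry can be told from emergent ones only indirectly

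*Protocol article*

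**What the plan says.** Safety is a stated aim: the Study design section describes a trial "aimed at evaluating the efficacy and safety of acupuncture for RLS patients", comparing acupuncture with sham. The Safety assessments section names one instrument: "All adverse effects will be assessed by the Treatment Emergent Symptom Scale". The same section sets the adverse event window as "from the time the subject signed the informed consent form to the time of the last follow-up", whatever the cause, and adds: "We will record the time point, severity, measures taken, whether it is related to treatment, and prognosis of adverse events".

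Table 1 marks TESS in Weeks 1, 2, 3 and 4 and nowhere else. It marks IRLSS, RLSQoL, ISI, PSQI, HAMD and HAMA at Week 0, and it also puts consent, clinical interview, physical examination and laboratory test there. The 12 sessions lie in the treatment phase, Weeks 1 to 4.

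On the disease itself, the Introduction describes night-time symptoms "causing difficulty falling asleep and increasing the number of night awakenings, and then fatigue, memory loss, depression, and blood pressure fluctuations".

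**The concern.** To call a symptom treatment-emergent is to compare it with the patient's state before treatment. On TESS that state is never recorded. The disease brings complaints that a general symptom scale may well pick up, so a long-standing complaint and a new one can look alike at the first reading in Week 1.

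Two consequences are possible. Each arm's TESS rate may be inflated by background RLS symptoms. And if acupuncture relieves those symptoms more than sham does, as the Sample size section hypothesizes for IRLSS (a 4-point advantage), fewer symptoms remain to be scored in the acupuncture arm. Part of an efficacy difference could then be reported as a safety difference. Randomization balances symptoms at entry but not their later relief, and blinding of patients and assessors does not change that either.

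**Working it through.** **1. The schedule, side by side (Table 1)**

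| | Week 0 | Weeks 1–4 | Months 1, 3 |
|---|---|---|---|
| Consent (opens the adverse event window) | yes | – | – |
| Six clinical scales | yes | Weeks 2 and 4 | yes |
| Treatment sessions | – | 12 | – |
| TESS | no | every week | no |

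The window opens at Week 0 and the instrument starts at Week 1. Table 1 does not say on which day of Week 1 TESS is given, so nothing secures a reading before the first session.

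**2. What else could identify a pre-existing symptom**

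- Recorded time point of each event: for a long-standing complaint first asked about in Week 1, this rests on recall.
- Judgement of relatedness to treatment.
- Week 0 ISI and PSQI (sleep), HAMD and HAMA (mood), interview and examination. These are different instruments, and the article states no rule linking them to TESS items.

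Separation is therefore possible, but indirect.

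**3. Illustration of direction**

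The article states no symptom rate, so there is no figure to reproduce and every input here is assumed. Let p be the share with an overlapping TESS symptom at entry, r the share of those resolved by Week 4, and e the risk of a truly new symptom. The share with any such symptom present at Week 4 is

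R = p(1 − r) + [1 − p(1 − r)] × e.

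Take r = 0.40 under acupuncture, r = 0.20 under sham and e = 0.05 in both arms, so the true safety difference is 0. For p = 0.30:

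- acupuncture: 0.18 + 0.82 × 0.05 = 22.1%
- sham: 0.24 + 0.76 × 0.05 = 27.8%
- difference: −5.7 points

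| p | Acupuncture | Sham | Difference (true: 0) | Difference if e is 10% v 5% (true: +5) |
|---|---|---|---|---|
| 30% | 22.1% | 27.8% | −5.7 | 26.2% − 27.8% = −1.6 |
| 50% | 33.5% | 43.0% | −9.5 | 37.0% − 43.0% = −6.0 |
| 80% | 50.6% | 65.8% | −15.2 | 53.2% − 65.8% = −12.6 |

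In the last column a real excess of new symptoms under acupuncture changes sign.

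**4. How far this depends on the counting rule and on relief**

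- *Equal relief (r = 0.20 in both arms, e = 0.05 in both):* 27.8%, 43.0% and 65.8% in each arm, difference 0. The rates are inflated, but no false difference arises.
- *Ever present in Weeks 1–4, with entry symptoms still there at the Week 1 reading:* the rate is 1 − (1 − p)(1 − e). For p = 0.30 this is 1 − 0.70 × 0.95 = 33.5% in both arms, whatever is relieved later. Again the rate is inflated and the difference is 0.
- *Only symptoms with onset after treatment began, applied strictly:* the rate is e. The differences return to 0 and +5 points.

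The false advantage therefore needs three things together: overlap between TESS items and RLS symptoms, unequal relief, and a count of symptoms present at a visit.

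**The case against.** A reader might infer that pre-existing and emergent symptoms cannot be separated at all, or that entry symptoms will be scored as adverse effects in Week 1. The article does not support either reading. Its definition covers only reactions occurring after consent, so fatigue or low mood that predates consent is not an adverse event on its terms. Time point and relatedness are recorded, and Week 0 already includes an interview, an examination and scales for sleep, depression and anxiety.

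A reader might also take the figures above as the expected bias. They are not. The article does not list the TESS items, say whether TESS rates any symptom present or only emergent ones, or state how TESS will be summarized by arm. The eligibility criteria, which require a normal neurological examination and exclude severe mental symptoms and serious organic disease, narrow the overlap further. A count over all four weeks would show no false difference in the illustration.

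Finally, a rule for counting new or worsened items may properly sit in an analysis plan or full protocol that is not shown, and its absence from the article is no fault. All of this stands.

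What it does not answer is the schedule. A later analysis plan can define a change from baseline, but it cannot supply a TESS baseline that was never collected.

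**Conclusion.** The point holds as a gap in the assessment schedule. The instrument named for all adverse effects has no pre-treatment reading, although the adverse event window opens at Week 0. Separating emergent from pre-existing symptoms then rests on recall, judgement and other scales.

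The likely direction of any distortion is inflated rates in both arms and, if acupuncture relieves symptoms more and symptoms are counted as present at a visit, an apparent safety advantage for acupuncture. The size cannot be derived from the documents; the 5.7 to 15.2 points rest wholly on assumed rates and that counting rule. No between-arm bias follows from equal relief, or from strict use of onset. This is a cheap improvement to a safety comparison, not a flaw that invalidates it.

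**What to change.** In Table 1, add a TESS mark at Week 0, to be completed before the first session. In Safety assessments, state that a TESS item counts as treatment-emergent only if it is new or more severe than at Week 0, and that these counts are compared between arms.

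The cost is a few minutes per patient at a visit where six scales are already given, plus one sentence of text. Patients already treated would lack the value. For them the Week 0 interview and scales are the only substitute, and the report should say how many are affected.

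Extending TESS to the Month 1 and Month 3 visits is a separate matter and would not supply the missing baseline.

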### Randomization and blinding

Statisticians will use SPSS V.26.0 to generate a random-number list, and the patients will be randomized into the treatment group or the control group in a 1:1 ratio according to the order in which they have signed the informed consent. The random number and treatment plan will be printed out and put into sealed opaque envelopes. The envelopes will be numbered, and the enrolled patients will be randomly grouped by matching the numbers on the envelopes in order of inclusion. During the trial, the generation of the random number list, patient recruitment, acupuncture treatment, outcome measurement, and data analysis are all conducted by specialized personnel who do not exchange information with each other. Only the acupuncturist will know the allocation. The patients and other researchers will be blinded to assignments.

### Data collection and management

To ensure standardization, researchers will be trained uniformly before the trial, including questionnaire survey, clinical treatment, indicator detection, data collection, and management. The questionnaire survey will be arranged for researchers to complete, and the researchers must fully understand the contents of the questionnaire. During the experiment, researchers should carefully implement informed consent and patiently explain the study to the subjects so that they can fully understand and cooperate with the study. Questionnaire investigators will perform patient interpretation and truthfully record the patient’s questionnaire situation. Clinical treatment will be carried out by fixed doctors, and the operation methods of acupuncture and sham acupuncture will be unified. In the process of treatment, clinicians will standardize operations, try to avoid unnecessary communication with the patients, and not inform the patients of the treatment plan. fMRI and PET-CT scans will be performed by stationary personnel using the same scanner and analyzed.

Data will be collected at the baseline (1 week before the first intervention), during the intervention (the second week of the intervention), after the intervention (at the end of the intervention), at 1-month follow-up, and at 3-month follow-up. We will collect data at baseline and after the intervention, including the following assessments: the IRLSS for evaluating the severity of RLS, the RLSQoL for reflecting the quality of life of patients with RLS, the ISI for reflecting the severity of insomnia, the PSQI for assessing sleep quality, the HAMD for reflecting the depressive mood of the subjects, the HAMA for reflecting the anxiety mood of the subjects, and the PSG for analyzing the sleep process and sleep structure throughout the night. Additionally, we will conduct PET-CT and fMRI scans of the brain.

The data we will collect during the second week of the intervention, at 1-month follow-up, and at 3-month follow-up will include IRLSS, RLSQoL, ISI, PSQI, HAMD, and HAMA. Data entry and management will be completed by the data manager, and data records will be timely, accurate, complete, and standardized. The data manager will use software for data entry and management. After the data manager confirms that the database is established correctly, the main researcher and statistical analyst will lock the data. The research process will be kept strictly confidential, and the locked data file will not be altered.

### Statistical analysis

Data analyses will be performed with the use of the statistical software SPSS V.26.0 (IBM SPSS Statistics, IBM Corp, Somers, NY, USA). Statistical analysis will be conducted by two analytical researchers independent of the experiment, following the principle of intention-to-treat (ITT) analysis. In this study, we plan to adopt a comprehensive strategy for handling missing data. Firstly, we will identify the mechanisms of data missingness, distinguishing between Missing Completely At Random (MCAR), Missing At Random (MAR), and Missing Not At Random (MNAR). We took preventive measures against data loss through carefully designed study procedures and data collection protocols, resorting to imputation techniques when necessary to maintain dataset integrity. Additionally, we plan to conduct sensitivity analyses to assess the impact of different missing data assumptions on study outcomes. Specifically, we will utilize Latent Growth Modeling (LGM) to estimate missing data under MAR and MNAR conditions, comparing results from different models to examine the robustness of our conclusions. Through these methods, we aim to ensure the reliability and validity of study results even in the presence of incomplete data. For the measurement data that conform to the normal distribution and homogeneous variance, the mean ± standard deviation (SD) will be used to describe the discrete tendency and central tendency. The comparison between the two groups will be performed by the independent-samples *t* test. Comparisons at multiple time points will be made using repeated-measure analysis of variance. Measurement data that do not conform to the normal distribution will be described by median and interquartile range. Comparison between the two groups will be conducted using the Mann–Whitney *U* rank-sum test. The comparison of multiple time points will be based on the generalized estimating equation (GEE). Enumeration data will be expressed by frequency (n) and constituent ratio (%). Comparison between the groups will be performed by the X² test. When the data do not meet the conditions of the X² test, the Fisher’s exact probability method will be used. In this study, all statistical tests will be performed two-sided, and P<0.05 will indicate that the difference is statistically significant.

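### The observed distribution chooses the IRLSS analysis method, and the repeated-measures ANOVA has no stated link to the missing-data plan; one prespecified mixed model would settle both

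*Protocol article*

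**What the plan says.** All the relevant text is in the Statistical analysis section of the protocol article.

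- **Principle.** The analysis is to be done "following the principle of intention-to-treat (ITT) analysis".
- **Missing data.** As a first step, "we will identify the mechanisms of data missingness, distinguishing between Missing Completely At Random (MCAR") from MAR and MNAR. Imputation follows in conditional terms: "resorting to imputation techniques when necessary to maintain dataset integrity". Latent growth modelling (LGM) under MAR and MNAR is planned as a sensitivity analysis.
- **Branch 1.** "For the measurement data that conform to the normal distribution and homogeneous variance", the plan says: "The comparison between the two groups will be performed by the independent-samples" t test. It then says: "Comparisons at multiple time points will be made using repeated-measure analysis of variance".
- **Branch 2.** For non-normal data: "Comparison between the two groups will be conducted using the Mann–Whitney" test. For the longitudinal part: "The comparison of multiple time points will be based on the generalized estimating equation (GEE").

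The IRLSS is measured five times: at baseline, Week 2, Week 4, and 1 and 3 months after treatment (Table 1; Data collection and management). The Sample size section rests on a 4-point mean difference, SD 7.26 and 15% loss.

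The section does not say whether the ANOVA or GEE runs on imputed data. It does not say whether baseline is a level of the time factor or a covariate, or which effect or visit carries the treatment comparison.

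**The concern.** Three features of the stated text cause difficulty.

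1. **Method chosen by the data.** A check on the trial's own results decides whether the arms are compared on means or on ranks. These are different quantities. The trial is sized on a mean difference, which Mann–Whitney does not estimate.
2. **ANOVA and incomplete patients.** Classical repeated-measures ANOVA needs a complete profile over all visits it includes. Without imputation it becomes a completer analysis, which sits badly with ITT. The imputation clause has no trigger, no method and no link to the ANOVA.
3. **Missingness assumptions.** Ordinary unweighted GEE is generally valid only under MCAR, whereas the plan's own sensitivity work treats MAR and MNAR as live possibilities. The step meant to identify the mechanism cannot do so, because MAR and MNAR can fit the observed data equally well.

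At stake are a result that may depend on who dropped out, a primary method open to choice once data are in, and precision given up by not adjusting for baseline.

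**Working it through.** **Inputs from the document.** Difference 4 points, SD 7.26, two-sided α = 0.05, stated power 0.90, 52 per arm before loss, 15% loss, 62 per arm, 124 in total.

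**Assumed, not in the document.** Correlation ρ between IRLSS visits of 0.3–0.7 (equal for all pairs), and the dropout patterns described below.

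**Step 1. The plan's own figure.** n = 2(z₁ + z₂)²σ²/δ², with σ²/δ² = 52.71/16 = 3.294.
- Power 0.90: 2 × (1.960 + 1.282)² × 3.294 = 69.2, so 70 per arm.
- Power 0.80: 2 × (1.960 + 0.842)² × 3.294 = 51.7, so 52 per arm; 52/0.85 = 61.2, so 62.

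The stated 52 and 62 match 80% power, not 90%. That is a separate matter, but it makes 80% the right reference for what follows.

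**Step 2. Patients affected by deletion.** 124 × 0.15 = 18.6, about 19. That leaves 105.4, or 62 × 0.85 = 52.7 per arm. Isolated missed visits among patients not lost would lower this further.

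**Step 3. Gain from baseline adjustment at one visit.** The residual SD is 7.26 × √(1 − ρ²), and the standard error is that SD × √(2/52.7). Power is Φ(4/SE − 1.96).

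| Analysis | Residual SD | SE | 4/SE | Power |
|---|---|---|---|---|
| Unadjusted t test | 7.26 | 1.414 | 2.83 | 0.81 |
| Adjusted, ρ = 0.3 | 6.93 | 1.349 | 2.97 | 0.84 |
| Adjusted, ρ = 0.5 | 6.29 | 1.225 | 3.27 | 0.90 |
| Adjusted, ρ = 0.7 | 5.18 | 1.010 | 3.96 | 0.98 |

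With the noncentral t distribution in place of the normal, the four values are 0.80, 0.84, 0.90 and 0.98.

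**Step 4. Bias from analysing completers only.** Simulation with 4,000 trials per setting, 62 per arm, a true difference of −4 from Week 2 onward, and about 14–16% dropout after Week 2.

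| Dropout pattern | ρ = 0.3 | ρ = 0.5 | ρ = 0.7 |
|---|---|---|---|
| Depends on Week 2 score in sham only; completers | −3.68 | −3.45 | −3.27 |
| Same pattern; MAR-based estimate | −3.99 | −3.97 | −3.99 |
| Depends on score equally in both arms; completers | −3.98 | −3.99 | −4.00 |

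The sham-only bias is therefore about 0.3 to 0.7 points towards no effect. With equal dependence there is none.

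Extreme case: every one of the worst 15% of sham patients at Week 2 leaves, and acupuncture losses are random. Bias = ρ × SD × φ(1.036)/0.85. Here φ(1.036) = 0.233 and 0.233/0.85 = 0.274, so at ρ = 0.6 the bias is 0.6 × 7.26 × 0.274 = 1.19 points, again towards no effect.

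**Step 5. Baseline as an outcome level.** If baseline were one of five time levels, the effect were a constant 4 points at the other four, and the group main effect were the test, the tested difference would be 4 × 4/5 = 3.2 points. The document states neither condition.

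**The case against.** The strongest defence has four parts.

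- **The plan has a missing-data strategy.** LGM under MAR and MNAR is named, with results compared across models. Which dataset feeds the ANOVA may be settled in a fuller document that is not shown. This stands in part: the plan does not contradict itself. But LGM is offered as a sensitivity analysis, so it does not repair the main analysis.
- **The t test already matches the sizing.** The two-sample t test targets the same mean difference as the sample-size formula, and the ANOVA is named only for several time points. This stands for the normal-data branch. It fails in the other branch, and the t test as stated is unadjusted.
- **The 15% loss is already in the sample size.** True for numbers. Inflation does not protect against selective loss.
- **GEE keeps incomplete patients.** Correct. The only objection there is the MCAR requirement.

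A reader might go further and infer that the ANOVA dilutes the effect and has low power. The text does not support this, because it neither makes baseline a time level nor names the group main effect as the test. Nor is low power general. At ρ = 0.6 with 52.7 completers per arm, and assumed effects of 0/2/4/3/2 over the five visits, the main effect has 47% power but the group-by-time interaction 76%. With 0/2/4/4/4 the figures are 67% and 91%. Interaction power falls to 49% and 67% at ρ = 0.3, so the answer turns on assumptions that the document does not give.

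**Conclusion.** The point holds in a limited form. Three things follow from the text itself: the method switches on the observed distribution, imputation is not linked to an ANOVA that needs complete profiles, and the plan claims to identify a mechanism that observed data cannot identify. Deletion of about 19 patients follows only if the ANOVA runs on unimputed data, so this is an unresolved gap with ITT rather than a proven breach of it.

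The size is moderate and rests on assumption. Completer bias ranges from none to about 0.3–0.7 points under moderate sham-only dropout, with about 1.2 of the 4 points as an extreme case at ρ = 0.6. In these scenarios it shrinks the effect rather than creating one. The precision given up by leaving out baseline is 80% against 84–98% power for ρ of 0.3–0.7. The change should be made before database lock, but the point does not by itself invalidate the trial.

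**What to change.** Replace both branches for the IRLSS by one prespecified likelihood-based mixed model, which SPSS MIXED can fit:

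- **Outcome:** post-baseline IRLSS at Weeks 2 and 4 and at the 1- and 3-month follow-ups.
- **Fixed effects:** treatment, visit, treatment × visit, baseline, baseline × visit.
- **Covariance:** unstructured.
- **Patients:** all randomised patients with any post-baseline value, in the arm assigned.
- **Primary result:** the treatment contrast at one named visit. End of treatment (Week 4) is the natural choice, but the document names none, so the sponsor must state it.

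Use this model whatever a normality check shows. With about 50 per arm, a comparison of means on a bounded sum score does not need that gate. Keep rank tests as sensitivity analyses only.

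Replace the step that identifies the mechanism by a statement that MAR is the primary assumption. Keep the planned LGM, or a delta-adjusted analysis, as the MNAR sensitivity analysis. If imputation is retained, state its method and which analysis it feeds.

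The cost is a change of protocol or SAP wording and slightly more analysis work. The software stays the same, and no new data or visits are needed.
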